## Abstract

**Background:**

Healthcare-associated infections affect 10% of patients in Canadian acute-care hospitals and are significant and preventable causes of morbidity and mortality among hospitalized patients. Hand hygiene is among the simplest and most effective preventive measures to reduce these infections. However, compliance with hand hygiene among healthcare workers, specifically among physicians, is consistently suboptimal. We aim to first identify the barriers and enablers to physician hand hygiene compliance, and then to develop and pilot a theory-based knowledge translation intervention to increase physicians’ compliance with best hand hygiene practice.

**Design:**

The study consists of three phases. In Phase 1, we will identify barriers and enablers to hand hygiene compliance by physicians. This will include: key informant interviews with physicians and residents using a structured interview guide, informed by the Theoretical Domains Framework; nonparticipant observation of physician/resident hand hygiene audit sessions; and focus groups with hand hygiene experts. In Phase 2, we will conduct intervention mapping to develop a theory-based knowledge translation intervention to improve physician hand hygiene compliance. Finally, in Phase 3, we will pilot the knowledge translation intervention in four patient care units.

**Discussion:**

In this study, we will use a behavioural theory approach to obtain a better understanding of the barriers and enablers to physician hand hygiene compliance. This will provide a comprehensive framework on which to develop knowledge translation interventions that may be more successful in improving hand hygiene practice. Upon completion of this study, we will refine the piloted knowledge translation intervention so it can be tested in a multi-site cluster randomized controlled trial.

## Background

Healthcare-associated infections are ranked by the World Health Organization as one of the top 10 causes of hospital deaths worldwide [1]. In Canada, they are the most common serious complication of hospitalization, affecting 10% of all patients in acute-care hospitals [2] and are the fourth leading cause of death [3]. Healthcare-associated pathogens that can lead to infection are transmitted through direct and indirect contact, droplets, air, and the contaminated hands of healthcare workers (HCWs), the latter being the most common vehicles of transmission in most settings [4]. Microorganisms are known to survive on hands for up to 60 minutes following contact with a patient or contaminated surface. Hand contamination increases with increasing time spend providing direct patient care, in the absence of appropriate hand hygiene [4].

Hand hygiene, defined as the act of washing one’s hands with soap and water or disinfecting them with an antiseptic agent, is the single most successful and cost-effective means of preventing healthcare-associated infections, as well as an effective means of preventing illness in the community that may lead to hospitalization [5-8]. Hand hygiene, before and after all patient or patient environment contact, before aseptic procedure, and/or after bodily fluid exposure, is recommended in all published infection control and public health guidelines and is considered the standard of care for all HCWs [5-10]. Yet many studies document that HCWs’ compliance with hand hygiene recommendations is consistently less than 50% [6,11-15], with compliance among physicians routinely lower than that of other HCWs [16-19]. Locally, at the Ottawa Hospital (proposed for this study), physician hand hygiene compliance rates have increased significantly from 14–17% between 2004–6 to 65–69% in March 2011. In spite of this increase, however, physician compliance continues to lag behind that of most other occupational groups and is below the corporate goal of 80%.

### Interventions to improve hand hygiene compliance

In 2010, Gould and colleagues [20] conducted an update of the 2007 Cochrane systematic review [21] on interventions to improve hand hygiene compliance in patient care. A total of four studies are included in the review: two from the original review and two from the update. Interventions tested included substitutions of products and different multifaceted campaigns that involved different levels of involvement by HCWs. Success in improving hand hygiene compliance was inconsistent across the four studies. The authors concluded that we lack sufficient research evidence to know which strategies improve hand hygiene compliance and that robust research is needed to further explore ‘the effectiveness of soundly designed and implemented interventions to increase hand hygiene compliance’ [20]. Most recently, Fuller and colleagues conducted a cluster randomised controlled trial of a behaviourally designed feedback intervention in 60 hospital wards across England and Wales that were implementing a national hand-hygiene campaign [22]. Findings revealed that the intervention, which coupled feedback to personalized action planning (compared to routine care), produced moderate and significant sustained improvements in hand-hygiene compliance [22]. While this study indicates promising effects for the use of behaviourally designed feedback interventions to improve hand hygiene compliance, further implementation studies are required to determine the intervention’s effect in different settings and contexts.

### Barriers and enablers to physician hand hygiene compliance

Reasons for low hand hygiene compliance by HCWs, and physicians specifically, are poorly understood. Studies investigating HCWs generally have reported a range of barriers, including environmental barriers (*e.g*., lack of access to sinks, difficulty of locating products, empty dispensers, dispensers and time constraints) and personal barriers (*e.g*., attitudinal beliefs, skin irritation from repeated hand washing) [23,24]. Using a behavioural theory approach, Boscart and colleagues explored nurses’ perceived barriers and enablers to hand hygiene practice [25]. Nurses focused on immediate consequences; for example, they identified their personal safety and their families’ safety as a core source of motivation to perform hand hygiene. They also described the importance of individual feedback and self-monitoring in order to increase their performance. With respect to barriers specific to physicians, research is limited. In a recent survey of attitudes towards hand hygiene, physicians reported ‘remembering to perform hand hygiene’ and ‘high workload or feeling too rushed’ as their top barriers to hand hygiene compliance [26]. A second study, which surveyed a variety of HCWs including physicians, found environmental barriers to hand hygiene compliance to be dominant, including lack of soap, broken soap dispensers, and lack of paper towels [27]. Educational gaps in infection control training among physicians also exist [17,18,28,29]; however, strategies effective for improving infection control practices of other HCWs have had significantly less impact on physicians [30,31]. Additional barriers that are specific to physicians that have been identified/postulated include: a perception among physicians that their compliance is much better than it actually is [32,33]; the development of a more cavalier attitude towards infection control as clinical experience increases, with an associated drop in compliance rates [30,34,35]; the lack of positive role models among physicians who are part of a healthcare team [35-37]; and, the local (*e.g*., unit, hospital) culture of patient safety [38].

In summary, the barriers and enablers to physician hand hygiene compliance and effective interventions to improve their compliance have not been well explored. To our knowledge, no studies have specifically addressed physician hand hygiene compliance using a behavioural theory approach that encompasses both barrier and enabler assessment, followed by intervention design based on these assessments. Therefore, the aims of this study are, first, to identify the barriers and enablers to physician hand hygiene compliance, and then to develop and pilot a theory-based knowledge translation intervention to increase physicians’ compliance with best hand hygiene practice.

### Guiding framework

Our goal is to develop and evaluate a theory-based, knowledge translation intervention to provide practical guidance about how to improve physician hand hygiene compliance. However, the development and evaluation of complex interventions such as knowledge translation interventions raise specific methodological and conceptual challenges. We have therefore adopted the UK Medical Research Council Complex Interventions Framework (MRC Framework) [39,40], which provides an iterative phased approach to the development and evaluation of complex interventions. The MRC framework suggests that the evaluation of complex interventions should follow a sequential approach, involving:

1. Phase 0: problem and contextual assessment, and development of the theoretical basis for an intervention;

2. Phase 1: definition of components of the intervention (using modeling or simulated techniques and qualitative methods);

3. Phase 2: exploratory studies to further develop the intervention and plan a definitive evaluative study (using a variety of methods);

4. Phase 3: definitive evaluative studies (using quantitative evaluative methods, predominantly randomized designs); and,

5. Phase 4: studies evaluating the sustainability of complex interventions.

Campbell and colleagues suggested that Phases 0–2 should be considered part of a larger iterative activity rather than as sequential studies, and highlighted that the insights gained during these early phases can make a valuable contribution to the development of the basic science of knowledge translation [40]. Based upon current systematic reviews, it appears that many knowledge translation studies have involved definitive trials, with little evidence of preceding theoretical or modeling research [41]. As a result, the interpretation of the current evidence base on the effectiveness and efficiency of different strategies is problematic because we lack a theoretical base for conceptualizing decision-making and behaviour change processes in different stakeholder groups. As a result, it is difficult to apply this evidence across a variety of health settings because we cannot identify which interventions are most likely, in particular settings, to be effective or efficient in improving quality. Further, we have little understanding of the causal mechanisms of different interventions. In this study, we will adopt an iterative approach (as suggested by Campbell and colleagues [40]) to the development and evaluation of a knowledge translation intervention to improve physician hand hygiene compliance.

## Methods

In this study, we define hand hygiene as: any action of hand cleaning that removes visible soil and removes and kills any microorganisms on the hands. We propose to use state of the art approaches from knowledge translation science to, first, identify key factors that act as barriers and enablers to best hand hygiene practice by physicians and then develop and pilot a knowledge translation intervention focused on improving hand hygiene compliance by physicians that is based on the identified barriers and enablers.

The study will be subdivided into three phases to be executed over one year:

Phase 1: identification of barriers and enablers to hand hygiene compliance by physicians. This will include: key informant interviews with physicians and residents; nonparticipant observation of physician/resident hand hygiene behaviours during regular hospital hand hygiene audit sessions; and focus groups with hand hygiene experts (this Phase is equivalent to Phase 0 in MRC framework).

Phase 2: intervention mapping to develop a theory-based knowledge translation intervention to improve physician hand hygiene compliance (this Phase is equivalent to Phase 1 in MRC framework).

Phase 3: implementation and pilot of the knowledge translation intervention (this Phase is equivalent to Phase 2 in MRC framework).

### Phase 1: Identification of barriers and enablers to physician hand hygiene compliance

The purpose of Phase 1 is to identify and describe physicians’ beliefs and attitudes about hand hygiene and their perceptions of the multi-level factors that influence this behaviour. This will allow us to identify determinants of the evidence-practice gap (*i.e.*, why physician hand hygiene compliance is inconsistent); specific behaviors that need changing in order to increase physician hand hygiene compliance; and the specific targets to be addressed by our theory-based knowledge translation intervention. This necessary preliminary work will generate a thorough understanding of physicians’ perceptions of the multi-level determinants of the behaviours required to improve physician hand hygiene compliance. Our data will come primarily from semi-structured interviews with physicians and residents. We will supplement this data with non-participant observation of physicians’ and residents’ hand hygiene practices (during regularly conducted hospital hand hygiene audit sessions) and focus groups with hand hygiene experts.

### Semi-structured interviews with physician and residents

#### Study population and sampling

Key informants will comprise staff physicians and residents in medicine and surgery at two geographical campuses from a large Canadian urban hospital. Lists of all eligible physicians and residents (divided by campus [n = 2] and specialty [n = 2, medicine and surgery]) will be obtained. From this master list, six new lists will be created for sampling purposes: (1) physicians medicine campus 1, (2) physicians medicine campus 2, (3) physicians surgery campus 1, (4) physicians surgery campus 2, (5) residents medicine, and (6) residents surgery. Residents will not be separated by campus as they work equally across campuses. A quasi-experimental sampling strategy will be used to select key informants from each list. The lists of potential key informants will be arranged in ascending order with respect to the informant’s name (first, last name), with each informant being assigned a number. The first key informant will be chosen at random, and the subsequent key informants will then be selected according to regular intervals, known as periods. A period is determined by dividing the population size (N on the list) by the desired sample size (n that is 5 or 10, depending on the group). The Associate Director of Infection Prevention and Control of the hospital will inform the chosen key informants via email that they have been selected for the study. Key informants who agree to participate will be instructed to contact the study research assistant (SL), at which time they will be provided additional details on the study. If they remain willing to participate after this initial contact, a time will be arranged to conduct the interview. This selection process will be repeated until the required sample size is achieved.

In qualitative research, there are no hard and fast rules about sample sizes. Determining adequate sample size is ultimately a matter of judgment and experience in evaluating the quality of the information collected against the uses to which it will be put, the particular research method and purposeful sampling strategy employed, and the research products intended [42]*.* We will use the concept of ‘data saturation’ to determine when we have interviewed a sufficient number of key informants. In other words, we will conduct interviews until no new barriers or enablers to physician hand hygiene compliance are being identified. Based on the diversity of our sample, *i.e*., physicians with an increasing degree of clinical experience (residents and staff physicians) and two medical specialties requiring different clinical practices (medicine and surgery), we propose to conduct a minimum of 40 interviews (divided equally between specialty and campus, with equal representation among residents and staff physicians; see Table 1). We will employ a stopping criterion of three interviews. The stopping criterion refers to the number of interviews to be conducted per sampled group, without new themes or concepts emerging, before we can conclude that data saturation has been reached [43].

**Table 1 T1:** Key informant interview sample

**Key informant group**	**Minimum number of interviews to be conducted**				
	**Medicine**		**Surgery**		**Total Interviews**
	**Campus 1**	**Campus 2**	**Campus 1**	**Campus 2**	
Residents	10		10		20
Staff Physicians	5	5	5	5	20
Total Interviews					40

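### Sorting the informant lists by name gives the interval draw no control of seniority within a list; sorting by seniority would be a low-cost improvement, mainly for residents

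*Protocol article*

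**What the plan says.** The section on study population and sampling divides the eligible physicians and residents before any draw: "six new lists will be created for sampling purposes". Four lists hold staff physicians (medicine and surgery at each campus) and two hold residents (medicine, surgery). Each list is "arranged in ascending order with respect to the informant’s name (first, last name". Then: "The first key informant will be chosen at random, and the subsequent key informants will then be selected according to regular intervals, known as periods". The interval is found by "dividing the population size (N on the list) by the desired sample size (n that is 5 or 10, depending on the group". Those drawn may decline, and the draw is run again until the quota is filled.

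On sample size the same section says "we propose to conduct a minimum of 40 interviews", divided "with equal representation among residents and staff physicians; see Table 1". It bases this on the diversity of the sample and describes experience as "physicians with an increasing degree of clinical experience (residents and staff physicians".

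The background section on barriers and enablers lists, among the barriers identified or postulated for physicians, "the development of a more cavalier attitude towards infection control as clinical experience increases, with an associated drop in compliance rates".

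In the section on generating specific beliefs, beliefs are counted in four subgroups: staff and residents, each by medicine and surgery.

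**The concern.** Systematic sampling stratifies implicitly on the sort variable. A list sorted by a relevant characteristic yields a sample spread evenly along it. A list sorted by an irrelevant one yields, in effect, a simple random sample. Name has no plausible relation to hand hygiene, so the plan uses a method that could balance the sample and gains nothing from it.

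The characteristic that the document itself singles out is clinical experience, described as a gradient and not only as a step from resident to staff. Within the resident lists nothing controls training year, and within the staff lists nothing controls years in practice. With 5 or 10 informants per list, a training year can be absent by chance.

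The saturation rule does not fully cover this. It stops after three interviews in a sampled group without a new theme, and a training year that was never sampled cannot supply one. The interviews are the primary data for the intervention built in Phase 2, so a barrier typical of one stage of training could go unheard.

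**Working it through.** **The plan's own figure.** Two resident lists of 10 and four staff lists of 5 give 2 × 10 + 4 × 5 = 40, of which 20 are residents and 20 staff. This agrees with Table 1 and holds whatever the sort key.

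**Assumptions, since the documents give no figures.** Name is unrelated to seniority, so the interval draw behaves like a simple random sample without replacement. Residents fall into five equal training years, and staff into three equal career-stage bands. Resident list sizes run from 30 to 100. Acceptance runs from 25 to 100%.

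**Resident subgroup: one list, n = 10.** By inclusion-exclusion,

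P(at least one year absent) = Σ (r = 1 to 4) (−1)^(r+1) · C(5, r) · C(N − rN/5, 10) / C(N, 10)

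- N = 30: 0.3264 − 0.0146 + 0.0000 = 0.312
- N = 60: 0.4338 − 0.0337 + 0.0003 = 0.400
- N = 100: 0.4756 − 0.0436 + 0.0005 = 0.433

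The large-list limit is 0.477. With four equal years instead of five, the figure is 14 to 19% for lists of 40 to 100.

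**Staff subgroup: two campus lists, 5 from each.** With three equal bands in each list of size N,

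P(a band absent from both) = 3 · [C(2N/3, 5) / C(N, 5)]² − 3 · [C(N/3, 5) / C(N, 5)]²

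- N = 15 per list: 3 × (252/3003)² − 3 × (1/3003)² = 0.021
- Large lists: 3 × (2/3)^10 − 3 × (1/3)^10 = 0.052

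A single staff list of 5 misses a third far more often: 1 − 0.679 = 0.32 for N = 30, and 1 − 0.617 = 0.38 in the limit. Beliefs are not counted by campus, however, so the pooled figure is the relevant one.

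**Effect of sorting by seniority, residents.** Each of five equal years spans N/5 places, which is two intervals of N/10. If everyone drawn accepts, the draw takes two residents per year. Refusals break this pattern. The simulation used a circular interval draw of 10, with further draws among those not yet approached until 10 accept, for lists of 60 to 100 and 6,000 runs per setting. The chance of missing at least one of five training years was:

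| Acceptance | Sorted by name | Sorted by training year |
|---|---|---|
| 100% | 40–44% | 0% |
| 75% | 40–44% | about 10% |
| 50% | 40–44% | 24–25% |
| 25% | 41–44% | 38–39% |

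At 25% acceptance the smallest list sometimes ran out before 10 had accepted, so that row is approximate.

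**The case against.** The strongest reply is that nothing here is wrong. A random-start interval draw from a name-ordered list is standard and unbiased, and the protocol promises no finer control of experience than residents against staff. That stands, and it sets the weight of the point.

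Further mitigation also stands in part. Forty is a minimum, interviewing continues to saturation, and audit observation and expert focus groups look for further barriers. With all 20 residents pooled, missing any of five years has a large-list probability of only about 5.7%. But the belief counts keep medical and surgical residents apart, and each of those groups is a single list of 10.

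Several stronger readings are tempting and are not supported:

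- **That spread over experience as a whole is left to chance.** Separate lists and equal quotas fix the resident/staff contrast.
- **That staff coverage is poor because a list of 5 misses a third up to 38% of the time.** The staff subgroups pool two lists, which brings this to about 2 to 5%.
- **That beliefs would be credited to the wrong group.** Group membership is known for every informant, so an absent career stage cannot move a belief from one subgroup to another.
- **That the random start causes a shortfall because it is not confined to the first interval.** A condensed article need not spell this out, and the draw is run again until the quota is met.
- **That sorting by seniority would secure the spread at no cost.** Participation is voluntary, and the documents do not say that the lists hold training year or years in practice.

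**Conclusion.** The point holds as a low-cost improvement to the sampling method. The sort key is stated in the text, it bears no relation to the behaviour under study, and a better key follows from the document's own background section. The gain lies mainly in the two resident subgroups, where a name-ordered draw leaves out at least one training year with a probability of about 31 to 43%. For staff subgroups the risk is already small.

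These sizes rest on assumed list sizes, five equal training years and three equal staff bands. The benefit depends on acceptance: it is large if most of those approached agree, about 16 to 19 percentage points at 50% acceptance (40–44% less 24–25%), and slight at 25%. No contradiction or bias is alleged.

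**What to change.** In the section on study population and sampling, change the sort key. Where the hospital's lists hold the information, order each resident list by training year and each staff list by years in practice, with name only as a tie-break. Keep the same random start, interval and n.

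The cost is one extra column on the lists, if it can be obtained, and one changed sentence. No interviews are added. If seniority is not available, name order can stay.
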